### 4.1. Interventions

#### 4.1.1. Exercise and Neuromodulation Protocol

The experimental group will engage in 90 min sessions, structured into three distinct blocks. In the initial two treatment blocks, the participants perform core stabilization exercises and general strength training, incorporating forced expiration to ensure proper transverse abdominal muscle activation. This approach aims to mitigate the adverse effects associated with increased intra-abdominal pressure. As outlined by Capel-Alcaraz et al. [27], multi-joint exercises for both the upper and lower limbs will be performed using elastic bands or free weights, involving trunk stabilization with abdominal activation during the first 30 min of the session. The session will be initiated with a 10 min mobility and activation block. In accordance with the protocol described by Virtuoso et al. [28], the strength training will adhere to the program established by the American College of Sports Medicine [29]. The exercises will be performed in a rotating sequence, beginning with larger muscle groups to facilitate gradual acclimatization to weight and sessions. As outlined by Helms et al. [30], the rate of perceived exertion (RPE) will be employed as a method to monitor the perceptual responses to training and assess effort during workouts. Zourdos et al. [31] suggest an RPE of 7–10, with a repetition in reserve (RIR) of 3 for resistance strength exercises and subsequent metabolic adaptations. Each set will consist of 10–12 repetitions, with the objective of attaining an RPE of 7–10 based on individual capabilities. Regardless, the number of repetitions will be approximate, with the primary emphasis being on achieving the specified RPE to ensure the intended muscular stimulus (Table 1).

Section 3 focuses on the regulation of anticipatory postural adjustments through the Proprioceptive Postural Reeducation Perineal Method (5P LOGSURF). This method aims to enhance the striated PFM by utilizing reflexive responses associated with sensorimotor control, body awareness, and balance. The exercises will be performed on an unstable oak wood platform that promotes anticipatory muscle activation and continuous postural adjustments. Participants will engage in 30 min sessions divided into two phases, as outlined by Fuentes-Aparicio et al. [15].

##### Neuromodulation Protocol

A protocol for electrostimulation of the posterior tibial nerve will be applied to trigger retrograde stimulation through the pelvic nerves linked to the spinal cord via the sacral plexus (S2–S3). The motor branches of the sacral plexus, which are parasympathetic fibers, end in ganglionic cells in the bladder wall. The procedure involves inserting a 34–36 gauge needle at a 60-degree angle to a depth of 3–4 cm, aiming for the posterior tibial nerve located approximately 5 cm (or three finger-widths) above the medial malleolus, just behind the tibia [32,33]. A dispersive adhesive electrode will be positioned near the plantar arch to serve as a ground, connected to the electrostimulator [32,34]. The protocol typically includes 10 sessions (ranging from 6 to 16), each lasting 30 min, conducted 2 to 3 times per week on non-consecutive days over a period of 3 months [34]. The current levels range from 0.5 to 9.0 mA at 20 Hz, with a pulse width of 200–500 ms, adjusted according to the patient’s tolerance, as indicated by discomfort, a tingling sensation in the bottom of the foot, or the bending of the big toe [20]. The patient will either sit or lie in the lateral decubitus position, with the treated leg supported on the table. Anatomical landmarks are employed to ensure precise needle placement 5 cm above the medial malleolus along the path of the posterior tibial nerve. Ultrasound guidance is used to accurately locate the nerve, providing real-time visualization of the anatomical structures and the needle path, thereby ensuring safe and minimally invasive access to deep peripheral nerves [35] (Figure 3). This method, often employed for peripheral nerve blocks in pain management, facilitates effective and targeted stimulations.

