## Abstract

**Introduction:** Overactive bladder (OAB) and urinary incontinence (UI) are prevalent, particularly in older adults, and affect quality of life. OAB involves urgency, frequency, nocturia, and urgency incontinence, often linked to involuntary detrusor contractions. Treatment guidelines recommend a stepwise approach, starting with pelvic floor muscle training (PFMT), followed by pharmacological or minimally invasive therapies, such as neuromodulation. However, the combined effects of PFMT and neuromodulation have not been well established. This study aimed to evaluate the impact of combining pelvic floor exercises with neuromodulation versus PFMT with sham neuromodulation or standard physiotherapy after a 12-week intervention in individuals with OAB and UI. **Methods/Materials:** A double-blind, randomized controlled trial was designed with three groups: PFMT + neuromodulation, PFMT + sham, and conventional physiotherapy (control) in a 1:1:1 ratio. This study followed the CONSORT guidelines and was registered at ClinicalTrials.gov (NCT06783374). The sample size was calculated using GPower^®^ software, assuming a Cohen’s effect size of 1.04, a power of 0.80, an alpha of 0.05, and a 15% dropout rate, totaling 63 participants (21 per group). Participants attended 24 sessions over 12 weeks (2 sessions per week). The interventions were based on previously validated protocols. **Outcomes:** The primary outcomes included health-related quality of life, pelvic floor muscle function, pain, adherence, and general health. The secondary outcomes included Incontinence Quality of Life questionnaire, 3-day bladder diary, International Consultation on Incontinence Questionnaire–Urinary Incontinence Short Form, kinesiophobia, and electromyographic data.

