### 2.4. Procedure

Once the groups have been assigned, four sample collections will take place at the following time points: Pre (baseline), Post_1month_, Post_3months_, Post_6months_ (Figure 2). All the participants will engage in 24 experimental sessions, each with a duration of approximately 60 min. At each assessment point, the studied variables will be monitored and recorded in the “Data Collection Notebook”. It has been created to systematically record both the primary and secondary outcome variables at each measurement point, in alignment with the study protocol.

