## 6. Program Feasibility and Safety: Attendance and Compliance

Adherence to exercise regimens for UI presents a multifaceted challenge, necessitating both behavioral modification and active patient engagement [56]. The process of behavioral change, essential for effective treatment adherence, is often intricate [57]. Empirical evidence indicates that home-based interventions are less efficacious compared to those supervised by a physiotherapist with specialized training [58]. Specifically, a structured exercise program for UI, when supervised during the treatment phase, is associated with higher adherence rates in both the short and long term [59]. Moreover, non-adherence to treatment poses a significant barrier to the success of UI interventions, with the efficacy potentially diminishing substantially if compliance falls below 80% [60]. Consequently, adherence is a critical determinant of the treatment efficacy and the enhancement of quality of life [61]. This study will implement an exercise regimen aimed at enhancing core stabilization and overall strength by incorporating forced exhalation to activate the transverse abdominal muscle, thereby mitigating the adverse effects of increased intra-abdominal pressure. In both the intervention and placebo groups, the training program will be conducted under direct supervision following posterior tibial nerve neuromodulation. Participants in the exercise groups will adhere to the prescribed training frequency, as monitored by the SIRAS scale [59].

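### The neuromodulation settings contradict themselves: the stated pulse is 4 to 10 times longer than a 20 Hz cycle, and 6–16 sessions cannot match 2–3 per week over 3 months

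*Protocol article*

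**What the plan says.** The electrical settings appear once, in the Neuromodulation Protocol within section 4.1.1: "The current levels range from 0.5 to 9.0 mA at 20 Hz, with a pulse width of 200–500 ms". The text adds that the settings are adjusted to the patient's tolerance.

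The stimulation schedule appears in the same paragraph: "The protocol typically includes 10 sessions (ranging from 6 to 16), each lasting 30 min", then "conducted 2 to 3 times per week on non-consecutive days over a period of 3 months". It carries a literature citation.

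Three other places bear on how often stimulation is given:

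- Abstract: "Participants attended 24 sessions over 12 weeks (2 sessions per week".
- Section 2.4: "All the participants will engage in 24 experimental sessions, each with a duration of approximately 60 min".
- Section 6, on the active and the placebo group: "the training program will be conducted under direct supervision following posterior tibial nerve neuromodulation".

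Section 4.1.2 describes the sham needle and the masking steps but gives no separate count or schedule for sham sessions. Nowhere does the article say that stimulation is given at only some of the 24 sessions.

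**The concern.** Two pairs of figures describing the experimental component do not fit together. A pulse cannot last longer than the cycle that contains it, so the pulse width and the frequency cannot both be right. A total of 6–16 sessions also cannot result from 2–3 sessions a week kept up for 3 months.

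The comparison of exercise plus neuromodulation with exercise plus sham is the only one in the trial that isolates neuromodulation. A reader who wants to repeat the active arm, or to judge whether sham exposure matched it, needs the settings and the number of sessions. Section 2.1 commits to reporting by TIDieR, and the discussion aims at standardised protocols. Neither can be achieved from figures that exclude one another.

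**Working it through.** **Inputs, all from the protocol article**

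- Frequency 20 Hz, pulse width 200–500 ms (section 4.1.1, Neuromodulation Protocol).
- Stimulation sessions: 10, range 6–16, 30 min each; 2–3 per week; 3 months (same place).
- Trial sessions: 24 over 12 weeks at 2 per week (abstract); 24 for all participants (section 2.4).

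**The plan's own figure**

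2 per week × 12 weeks = 24. The trial's session count reproduces.

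**Pulse width against frequency**

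- Cycle length = 1000 ms ÷ frequency = 1000 ÷ 20 = 50 ms.
- Pulse ÷ cycle = 200 ÷ 50 = 4 and 500 ÷ 50 = 10. The ratio must be below 1.
- Highest possible frequency = 1000 ÷ pulse width in ms: 1000 ÷ 200 = 5 Hz and 1000 ÷ 500 = 2 Hz. Both are below the stated 20 Hz.

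**Session count against rate and duration**

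Sessions = rate × weeks. Three months is tried as 12 and as 13 weeks.

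| Duration | 2 per week | 3 per week |
|---|---|---|
| 12 weeks | 24 | 36 |
| 13 weeks | 26 | 39 |

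The stated maximum of 16 is below the smallest implied total of 24.

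Turned round, weeks needed = sessions ÷ rate:

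| Sessions | At 3 per week | At 2 per week |
|---|---|---|
| 6 | 2 weeks | 3 weeks |
| 10 | 3.3 weeks | 5 weeks |
| 16 | 5.3 weeks | 8 weeks |

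Spread over 12 weeks, 6–16 sessions come to 6 ÷ 12 = 0.5 up to 16 ÷ 12 = 1.33 per week. That is below the stated 2–3.

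**Stimulation time under each reading, at 30 min per session**

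- Stated count: 6 × 30 = 180 min to 16 × 30 = 480 min.
- Stimulation at each of the 24 trial sessions: 24 × 30 = 720 min.
- Stated rate over 12 weeks: 24 × 30 = 720 min to 36 × 30 = 1,080 min.

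**The case against.** The arithmetic is not open to dispute, and nothing elsewhere in the article corrects either mismatch. The strongest reply concerns how far the point reaches.

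**The schedule may describe published practice.** It is hedged as what is typical and carries a citation, unlike the future tense used for what this trial will do. A range pooled over several published regimens need not multiply out. The trial's own schedule of 24 sessions is given twice, and section 6 is compatible with stimulation before every one of them. This stands in part: it softens the clash with 24 sessions. It does not remove the point, because the sentence sits under the trial's own intervention heading and is the only stimulation schedule given. If it is background, the article gives no explicit stimulation count. The mismatch between count, rate and duration remains either way.

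**Exposure need not vary within an arm.** A reader might set 180 min against 720 min and infer a fourfold spread between participants. The documents do not support that. The lower figure comes from the stimulation paragraph and the upper from the trial's overall session count, so the span lies between readings of the text. If the operators give every participant one schedule, the active–sham contrast is unaffected and the fault is one of description and replication.

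**Harm is not shown.** A reader might also infer a safety hazard, or that treatment must stop. The printed combination cannot be produced, so it cannot itself reach a participant. Current is limited to the stated range and adjusted to tolerance. The article does not give the device's operating settings, and a slip in a unit is plausible. This objection stands in full.

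The reply that a journal article condenses the full protocol does not help, because figures that exclude one another are not omitted detail.

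**Conclusion.** The point holds on the article's own figures, in two parts of different strength.

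1. **Pulse width and frequency: certain.** The stated pulse is 4 to 10 times the 50 ms cycle. At least one figure or unit is wrong, and the article does not show which. The conclusion needs no assumption beyond the printed values.

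2. **Session count: certain within the stimulation paragraph, less direct against the rest of the article.** A range of 6–16 cannot equal 2–3 per week over 3 months, whether that is 12 weeks (24–36) or 13 weeks (26–39). The conflict with the 24 trial sessions depends on reading the paragraph as this trial's instruction and not as a summary of the cited source.

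Planned stimulation is therefore 180–480 min on one reading and at least 720 min on the other, taking the stated 30 min per session. The article does not establish variable exposure within an arm, harm to participants or a need to suspend treatment.

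**What to change.** - Check pulse width and frequency against the device's operating settings and the cited source, and correct the Neuromodulation Protocol paragraph.
- Reconcile the abstract, section 2.4, the Neuromodulation Protocol in section 4.1.1 and section 6 to one stated number and frequency of stimulation sessions, the same for active and sham. If the typical-schedule sentence is background, label it so and state the trial's own schedule separately.
- Record for each participant the settings used and the number of active or sham sessions delivered.

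Which values are right is for the sponsor to establish, and none is proposed here. No hold on treatment is implied unless the check shows that the operating settings are wrong.

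The cost is a text correction, an ethics notification and a few fields on the session record. No additional participants or procedures are needed.

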## 3. Randomization and Blinding

The principal investigator, supported by a team of experienced physiotherapists with over a decade of expertise in neuromodulation and exercise therapy for UI, will oversee the implementation of the treatment protocol. Stratified randomization will be employed to ensure that the groups being compared are balanced in terms the specific levels of OAB-q SF [25]. The baseline OAB-q SF levels will be assessed before randomization, and the participants will be divided into two strata according to these levels, as outlined in the corresponding sections. One of the researchers will administer the interventions across all three groups, while the other will conduct the outcome assessments to maintain evaluator blinding. A block randomization design (block sizes of 4, 6, or 8) will be applied to ensure an equal number of participants in each group. To minimize the bias, the group allocation will be determined using a randomization table generated by an independent researcher using Excel. A double-blind design will be implemented to ensure objectivity.

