#### 4.1.2. Exercise + Sham Neuromodulation Protocol

In the sham group, a needle with a retractable handle, often utilized in experimental research alongside Streitberger and Kleinhenz placebo needles, will be used. These needles mimic insertion without piercing the skin and can remain in place for the duration of the intervention [36]. The design features a retractable mechanism that pulls the needle back into the handle when pressure is applied, creating the appearance of insertion (Figure 4). This arrangement allows the placebo needle to be swapped with a standard needle, preventing patients from visually distinguishing them. To ensure complete blinding of the treatment, patients will be placed in a lateral decubitus position to block their view of the procedure, preventing them from noticing the differences between the sham and intervention groups. Additional steps will include the use of antiseptic solutions and discarding the needles in visible waste containers to enhance the credibility of the procedure. These measures are consistent with the fundamental placebo principles for masking techniques, as described by Braithwaite et al., 2019 [36].

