### 5.2. Primary Outcome

#### The Overactive Bladder Questionnaire-Short Form (OAB-q SF)

The OAB-q SF is a concise, self-administered instrument featuring two scales that evaluate symptom distress and health-related quality of life (HRQoL) in individuals with overactive bladder [38,39]. This condition-specific questionnaire assesses symptom distress using 6 items and health-related quality of life (HRQoL) through 13 items. Patients rate each item on a 6-point Likert scale. The subscale scores are then combined and converted into a scale from 0 to 100. The symptom distress and HRQoL scales are inversely related: a higher symptom distress score reflects more severe symptoms, while a higher HRQoL score signifies better quality of life [25].

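### The lateral position meant to block the patient's view is optional in the active neuromodulation arm, so visual masking is not secured alike in the two needle arms

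*Protocol article*

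**What the plan says.** The Neuromodulation Protocol in Section 4.1.1 of the protocol article describes the active procedure. On posture it states: "The patient will either sit or lie in the lateral decubitus position, with the treated leg supported on the table". It mentions no screen, drape or other barrier to sight.

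Section 4.1.2 describes the sham procedure and gives posture a blinding purpose: "To ensure complete blinding of the treatment, patients will be placed in a lateral decubitus position to block their view of the procedure". The stated aim is "preventing them from noticing the differences between the sham and intervention groups". The same section describes a placebo needle that retracts into its handle, and says of it: "This arrangement allows the placebo needle to be swapped with a standard needle, preventing patients from visually distinguishing them". Antiseptic and visible disposal of needles are added to make the procedure credible.

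Section 3 claims blinding for the trial: "A double-blind design will be implemented to ensure objectivity". It also says that one researcher delivers the interventions in all three groups and another assesses outcomes. Section 5.2 describes the primary outcome: "The OAB-q SF is a concise, self-administered instrument featuring two scales".

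**The concern.** A sham procedure protects a comparison only if whatever the participant can perceive, apart from the active ingredient, is the same in both arms. Here the protocol names one such feature, the lateral position that hides the procedure. It requires that position in the sham section but leaves it optional in the active section.

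The contrast affected is the one that matters most for the neuromodulation question. The two needle arms share the supervised exercise programme (Section 6). The control arm differs in exercise content as well as in having no needle procedure (Section 4.1.3). Only active versus sham therefore isolates neuromodulation. The participant reports the primary outcome, so a participant who forms a view about her allocation can carry that expectation into the score. If active participants can see more of the procedure than sham participants, any resulting difference in expectation would probably favour the active arm.

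**Working it through.** No arithmetic applies: the point depends on no sample size, power or event figure. The check is a comparison of the two procedure descriptions, followed by a search of the rest of the article for anything that brings them into line.

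**Side by side**

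| Feature | Active procedure (4.1.1) | Sham section (4.1.2) |
|---|---|---|
| Position | Sitting or lateral decubitus | Lateral decubitus only |
| Purpose given for position | None related to blinding | To block the view and complete the blinding |
| Screen or other barrier to sight | None stated | None stated beyond position |
| Needle | Inserted to 3–4 cm | Retracts, does not pierce the skin, looks like a standard needle |

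**Step 1: does another section harmonise the position?** No. Section 3 claims double blinding and separates the treating from the assessing researcher, but says nothing about posture or sight lines. Section 6 says only that supervised training follows the needle procedure in both arms.

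**Step 2: which patients does Section 4.1.2 mean?** Two readings are possible.
- *Sham patients only.* The view-blocking position is then required in one needle arm and optional in the other.
- *Patients in both needle arms.* Section 4.1.2 then requires lateral positioning where Section 4.1.1 permits sitting, and the two sections contradict each other.

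On either reading the masking measure is not secured in both arms as the text stands.

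**Step 3: could position vary with allocation?** The article gives no rule for choosing between sitting and lying in the active arm. The researcher who delivers the treatment handles either a real or a placebo needle and so knows the allocation. Nothing prevents posture from differing systematically between arms. The opportunity recurs across the neuromodulation sessions, given as typically 10, with a range of 6 to 16.

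**Step 4: is there another visual safeguard?** Yes, the look-alike needle. The protocol does not treat it as sufficient, because Section 4.1.2 adds the view-blocking position after describing the needle, in order to complete the blinding.

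**The case against.** The best case against has four parts.

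*The active section is partly generic technique text.* It cites sources and gives typical ranges, and it permits sitting without requiring it. In practice every active patient may lie on her side. This stands as a limit on severity: what is shown is an unreconciled option, not a practice known to differ.

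*The look-alike needle already prevents visual recognition.* This stands in part. The needle is built to give the appearance of insertion. In a parallel-group trial nothing suggests that a participant sees the other procedure for comparison. A reader might infer that a seated active patient would know her treatment for sure. The documents do not support that: watching an apparent insertion does not settle allocation, and the article says nothing about what a seated patient can actually see.

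*Felt sensation may unblind in any position.* Active current is adjusted to discomfort, tingling in the foot or toe movement. That is a separate route, and harmonising position would not close it. It does not justify leaving this route open when closing it costs almost nothing.

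*A journal article condenses the full protocol.* This is decisive against one tempting extension. The active section says "Ultrasound guidance is used to accurately locate the nerve, providing real-time visualization of the anatomical structures and the needle path", and the sham section mentions no probe. A reader might infer that sham patients receive no ultrasound and that the visible routine differs at every session. The sham section also does not restate other shared details, such as the electrode, so silence about the probe shows nothing. The objection does not reach the position conflict, because there the article states both rules and they differ.

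**Conclusion.** The point holds as an internal inconsistency that leaves a blinding risk open. The protocol makes lateral positioning a masking measure and then makes it optional in the active arm, and no other section resolves this.

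The size of any bias cannot be computed. The article does not say how many active patients would sit, what they would see, or how far expectation moves the primary score. The number seated could be none or all of the active arm, so any figure for exposed patients would be a guess.

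The conclusion rests on two assumptions: that the active-arm text is meant to be followed as written, and that a patient's view of the procedure can influence her belief about allocation. The protocol makes the second assumption itself by adding the view-blocking position. The inconsistency should be corrected, since it touches the trial's key blinded contrast, but it does not by itself invalidate that contrast.

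**What to change.** Reconcile the Neuromodulation Protocol in Section 4.1.1 with Section 4.1.2 so that one positioning and view-blocking procedure governs both needle arms. Either of two forms would do: the same position in both arms, or the same screen over the leg in both arms whichever position is used. The choice of position belongs to the investigators.

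State also that the visible sequence is the same in both arms, from preparation through needle placement to disposal, and move the masking steps to a paragraph that expressly covers both.

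The cost is a few sentences of wording and possibly a drape. The downside is slightly less freedom in how the therapist positions the patient. Sample size, outcomes and analysis are unaffected.
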